### Measures

Our primary and secondary smoking-related treatment outcomes are based on recommendations by the Society for Research on Nicotine and Tobacco [61]. The primary treatment outcome will be continuous abstinence, defined as no smoking from the target quit date through the 3-month follow-up. The secondary treatment outcome will be biochemically-verified 7-day point prevalence abstinence at the 3-month follow-up, with participants who report that they are abstinent having their status confirmed via expired air carbon monoxide (CO) using a CoVita Smokerlyzer ^®^ monitor and, in cases where the breath sample suggests that they are currently smoking, by saliva cotinine using a NicAlert cotinine test strip. Participants who report no smoking, but whose CO level > 5 ppm or cotinine level > 10 ng/mL, will be coded as smoking. We acknowledge that there is a possibility of carbon monoxide false positives related to smoking other substances such as marijuana. We will probe further about marijuana use if a participant reports no smoking but biochemical data suggest otherwise [62]. In addition, we will utilize the reliable and valid smoking time line follow-back (TLFB) procedure [63] to collect detailed information on smoking patterns in the 30 days prior to the cessation counseling session (assessed at baseline) and the 30 days after the participants’ target quit date (assessed at follow-up). This will be used to examine intervention effects on the average number of cigarettes smoked per day.

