#### Power Considerations

A goal of this pilot study is to get an estimate of both the variability of the outcomes and of potential intervention effects so that we are better positioned to plan for the sample size for a future larger study [70]. To determine the necessary sample size for the larger study, we will determine what the clinically meaningful effects are for somewhat similar interventions from the literature. We will standardize such effects using the estimates of variability obtained with our pilot study data. For the pilot study, we plan to enroll up to 80 participants, with approximately 5–7 participants per group or cluster. We assume that 90% of them participate in the follow-up survey, based on our previous work [36], and assume a conservative interclass correlation (ICC) of 0.05. Under these assumptions, the effective sample size (ESS) at follow-up will be 36/(1 + 5*0.05) = 28.8 per condition. This provides 80% power to detect a moderate quit rate effect size (h = 0.72) for the difference between the two treatment conditions (alpha = 0.05).

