## Discussion

### Limitations and alternative methods considered

The proposed intervention focuses exclusively on cigarette smoking and is not designed to address the use of electronic nicotine delivery systems (ENDS), poly-tobacco use, or the co-use of tobacco with cannabis or other substances. However, we will be able to explore intervention effects on these other forms of substance use in our analyses. It should also be noted that we are not providing cell phones to participants while they participate in this study; rather, individuals must have a working cell phone that can receive text messages in order to participate. We will be monitoring the number of individuals who screen ineligible for this reason, or have a phone that is lost or stops working during the intervention, as indicators of the feasibility of using TMIs with this population.

In terms of the research design, we initially considered a design in which individuals would be randomly assigned to condition within agency. However, we decided against this design given concerns on the part of the research team and drop-in center staff about implementation challenges (e.g., clients perceiving that they were being refused services that other clients were getting) and the strong potential for contamination across conditions. A group-randomized design was a much better option for this evaluation in that it addressed both of these concerns. We will maximize the comparability of the intervention and control groups by: (1) having each drop-in center serve as both intervention and control site on an alternating basis; and (2) using the same procedures at each drop-in center to identify and recruit participants for the study. In addition, once the data are collected we will conduct preliminary analyses to determine whether the intervention and control groups differ on baseline characteristics. This step is necessary despite randomization because the randomization is not occurring at the individual level. If we observe considerable differences in the intervention and control groups, we will control for these with the addition of covariates into the regression models. We may also consider developing analytic weights using propensity score methods to balance the characteristics of the groups. As mentioned earlier, we will also control for any within-site effects by including site as a fixed effect (dummy coded) within the models.

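### Verified 7-day abstinence: as the coding rule is written, the confirmatory cotinine test can never overturn a positive CO result

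*Protocol article*

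**What the plan says.** The Measures section on smoking outcomes makes continuous abstinence the primary outcome. It then states: "The secondary treatment outcome will be biochemically-verified 7-day point prevalence abstinence at the 3-month follow-up". Verification has two steps. Everyone who reports abstinence gives an expired-air CO sample. A second test follows only for some: "in cases where the breath sample suggests that they are currently smoking, by saliva cotinine using a NicAlert cotinine test strip".

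The coding rule comes next: "Participants who report no smoking, but whose CO level > 5 ppm or cotinine level > 10 ng/mL, will be coded as smoking". The section then concedes a weakness of the first test: "We acknowledge that there is a possibility of carbon monoxide false positives related to smoking other substances such as marijuana". The response offered is: "We will probe further about marijuana use if a participant reports no smoking but biochemical data suggest otherwise". Nothing says what the answer to that probe does to the participant's code.

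Under Limitations and alternative methods considered, the intervention is described as "not designed to address the use of electronic nicotine delivery systems (ENDS), poly-tobacco use, or the co-use of tobacco with cannabis". Neither cannabis use nor e-cigarette use appears among the exclusion criteria under Participants.

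**The concern.** A second test that is run only after a positive first test normally serves to confirm or overturn the first. Here the two cut-offs are joined by *or*, so a participant who reaches the second test with CO above 5 ppm has already been coded as a smoker. The strip is taken but cannot alter that code.

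This matters because the section itself identifies who is harmed: people who have stopped cigarettes but smoke marijuana. They would be counted as smokers in the only biochemically verified outcome of the trial. The stated aims (Effects of the TMI on smoking behavior; Power Considerations) are to obtain effect-size and variability estimates for planning a larger trial, so a quit rate that is too low would be carried forward. Two analysts could also code the same participant, with high CO and negative cotinine, differently: one following the described sequence, the other the printed rule.

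**Working it through.** **Step 1: logic of the rule.** Inputs, all from the Measures section: CO is taken from all who report abstinence; cotinine only if CO suggests smoking; the cut-offs are 5 ppm and 10 ng/mL. The reachable cases are:

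| CO | Cotinine | Rule as printed | CO alone | Sequential rule |
|---|---|---|---|---|
| ≤ 5 ppm | not run | abstinent | abstinent | abstinent |
| > 5 ppm | ≤ 10 ng/mL | smoking | smoking | abstinent |
| > 5 ppm | > 10 ng/mL | smoking | smoking | smoking |

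The printed rule agrees with CO alone in every row. Only the middle row separates it from a rule in which cotinine decides, and that is the row into which a marijuana-related false positive falls if the participant has used no nicotine.

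The CO level that triggers the strip is not given as a number; 5 ppm is the only CO cut-off in the text. If the trigger were lower, cotinine could add smokers among those with CO at or below 5 ppm. It still could not remove anyone above 5 ppm.

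**Step 2: the plan's own figure.** Power Considerations gives "the effective sample size (ESS) at follow-up will be 36/(1 + 5*0.05) = 28.8 per condition". This reproduces: 80/2 × 0.90 = 36, and 36/1.25 = 28.8. The point does not depend on it. Only the 36 followed per condition is used below.

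**Step 3: size.** Let p be the true quit rate in an arm and f the share of true abstainers with CO above 5 ppm from marijuana. Then:

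- observed quit rate = p(1 − f)
- observed difference = (p₁ − p₂)(1 − f)
- risk ratio = p₁(1 − f) / [p₂(1 − f)] = p₁/p₂, unchanged
- abstainers miscoded per arm = 36 × p × f

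The document gives neither f nor expected quit rates. The values below are assumptions: true rates of 16% and 10%, f from 10% to 40%, equal in both arms.

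| f | Observed rates | Difference | Risk ratio | Odds ratio | Miscoded per 36 |
|---|---|---|---|---|---|
| 0 | 16.0% vs 10.0% | 6.0 points | 1.60 | (0.16/0.84)/(0.10/0.90) = 1.71 | 0 |
| 10% | 14.4% vs 9.0% | 5.4 points | 1.60 | (0.144/0.856)/(0.09/0.91) = 1.70 | 0.6 and 0.4 |
| 40% | 9.6% vs 6.0% | 3.6 points | 1.60 | (0.096/0.904)/(0.06/0.94) = 1.66 | 2.3 and 1.4 |

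The absolute rates and their difference shrink. The odds ratio, which is what the planned logistic regression estimates, barely moves.

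**The case against.** **It is a matter of wording.** The coding sentence may be meant as a list of cut-offs, one for whichever test is decisive, and the full protocol may hold the working rule. The authors may well have intended this. But the article does not leave the rule out. It prints a procedure and a coding rule with cut-offs, and read literally the rule cancels the purpose of the procedure. The sentence needs correcting whatever was intended.

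**Coding as smoking on either positive test is a legitimate conservative choice.** True in general. But if that were the aim, a strip taken only after a positive CO would serve no purpose, and the acknowledged false positives would simply be accepted. The text does not say so.

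**The consequences are small.** This largely stands. Only a secondary outcome of a pilot with up to 80 participants is affected, some analyses are to be descriptive, and both test results would be on record, so either coding can be applied later.

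**Stronger readings that the documents do not support.** A reader might infer that cotinine is useless because both arms receive patches. The supply is at most 8 weeks and follow-up is at 3 months, so overlap would need a late quit date or delayed or intermittent use. E-cigarette use is the more plausible interference. A reader might also infer a bias in the treatment comparison. One sample text to the TMI arm suggests staying away from alcohol or marijuana if these are triggers, so f could differ by arm: with 10% true quitting in both arms and assumed f of 20% (TMI) and 40% (control), the observed rates would be 8% and 6%. That is possible, but the document gives no figure to support a difference in f.

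**Conclusion.** The point holds, at moderate severity. As printed, the verification rule is equivalent to CO above 5 ppm alone (with 5 ppm as the trigger for the strip), and under any trigger a negative cotinine cannot reverse a CO above 5 ppm. The marijuana probe does not change this, because no coding consequence is attached to it. That conclusion rests on the text alone.

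The effect is to understate verified quit rates in both arms and their absolute difference by the unknown factor (1 − f), and hence the base rate passed to the larger trial. The size depends on f and on the true quit rates, neither of which is in the document. The calculation also assumes that f is the same in both arms and that no other misclassification occurs. Under those assumptions the relative effect is essentially preserved. A reader should not infer that the primary outcome is compromised: the section on effects on smoking behavior describes continuous abstinence as self-reported.

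**What to change.** Replace the coding sentence with the sequence that the section already describes. A participant who reports 7-day abstinence and has CO above 5 ppm is coded as smoking only if the confirmatory cotinine is above 10 ng/mL; CO above 5 ppm with cotinine at or below 10 ng/mL is coded abstinent. State what, if anything, the marijuana probe changes.

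Add two sensitivity analyses:

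- the CO-only coding that the present *or* rule produces;
- an alternative coding of participants who report recent e-cigarette or other nicotine use, including any late patch use. A positive cotinine says nothing about cigarettes in these participants, so they should be flagged.

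The cost is a rewritten sentence in the outcome definition and, if not already collected, survey items on patch and e-cigarette use in the past 7 days. No new test is needed. The downside is a slightly less strict main coding, which the CO-only sensitivity analysis makes visible.

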#### Effects of the TMI on other smoking-related outcomes

As a secondary focus, we will examine estimates of the intervention effect on proximal outcomes/mediators (i.e., factors associated with smoking and motivation to quit among young people experiencing homelessness [9] and areas of focus in the TMI) and assess trends. While the planned sample will not be large enough for detecting statistically significant mediation effects, it will allow us to produce estimates of the intervention effect on proximal outcomes/mediators and assess trends. We will adopt a similar modeling approach to the one just described, using a DID approach, since these variables will be measured at both baseline and follow-up.

#### Measures

*Normative perceptions* will be assessed by asking “Out of every 10 people your age without a regular place to stay, how many do you think smoke cigarettes?” (0 to 10; based on prior work [64]. *Smoking within the participant’s social network* will be assessed by asking about the proportion of friends who smoke (1 = *none* to 5 = *all*) [65]. *Frequency of tobacco sniping and cigarette sharing* in the past 30 days will be assessed with established items [11, 66]. *Coping expectancies of smoking* will be measured with the 4-item PROMIS Coping Expectancies of Smoking short form [67]. *Self*-*efficacy for quitting* will be assessed by a 14-item measure [68], and *perceived barriers to smoking cessation* will be assessed by a 13-item measure [69].

#### Power Considerations

A goal of this pilot study is to get an estimate of both the variability of the outcomes and of potential intervention effects so that we are better positioned to plan for the sample size for a future larger study [70]. To determine the necessary sample size for the larger study, we will determine what the clinically meaningful effects are for somewhat similar interventions from the literature. We will standardize such effects using the estimates of variability obtained with our pilot study data. For the pilot study, we plan to enroll up to 80 participants, with approximately 5–7 participants per group or cluster. We assume that 90% of them participate in the follow-up survey, based on our previous work [36], and assume a conservative interclass correlation (ICC) of 0.05. Under these assumptions, the effective sample size (ESS) at follow-up will be 36/(1 + 5*0.05) = 28.8 per condition. This provides 80% power to detect a moderate quit rate effect size (h = 0.72) for the difference between the two treatment conditions (alpha = 0.05).

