## Text messaging interventions (TMIs) may be a promising approach

A recent Cochrane meta-analysis of randomized controlled studies that had follow-ups of 6 months or longer found that TMIs increased quit rates by 50–60%, both when the TMI was compared to minimal support and when it was tested as an adjunct to other forms of cessation support [26]. While these studies were mostly based on general adult samples, with only four studies specifically targeting young adults, using a TMI for smoking cessation may be a promising approach for young smokers experiencing homelessness. Nearly universal cell phone ownership among young people experiencing homelessness [27] holds great potential for offering ongoing support for behavior change as an adjunct to face-to-face services. A recent study using text messaging for daily data collection among homeless young people found it to be both acceptable and feasible; for example, individuals reported that receiving the texts made them feel that someone cared about them and encouraged them to self-reflect on their life [28]. There is growing appreciation that cell phones are not a luxury for those experiencing homelessness, but rather a necessity in terms of helping them maintain social and service contacts [29, 30]. Indeed, a number of recent initiatives have focused on increasing homeless individuals’ access to mobile technology for these purposes [31].

A tailored approach to smoking cessation which combines a single group counseling session and nicotine replacement with a TMI that is tailored to the circumstances of young smokers experiencing homelessness and the key factors that are known to be particularly relevant to their smoking cessation [9] could help circumvent the formidable barriers to quitting in this population. Such a TMI adjunct to a group-based treatment can provide ongoing information and support for quitting. This is especially important in service environments where both resources and the window for intervening with these young people are limited. Of course, there is much to learn about the feasibility of using TMIs for young people experiencing homelessness. For example, their cell phones may be more prone to loss or theft, or limitations in terms of data plans and functionality (ability to access websites, staying charged). These types of issues will be examined in this pilot study.

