## Methods/design

### Overview

This pilot study involves a cluster cross-over randomized controlled design [32–34] with up to 80 current smokers who desire to quit and who are recruited from three drop-in centers serving young people experiencing homelessness in the Los Angeles area. Two of the drop-in centers are approximately a two mile drive from each other, with the third drop-in center being approximately a 10–15 mile drive from the others. The unit of analysis will be the individual, but individuals will be assigned to groups (standard care alone vs. TMI adjunct) based on the drop-in center where they are seeking services. All participants will receive standard care: a 30-min group-based smoking cessation counseling session and free nicotine replacement. Half of these smokers will then also receive the TMI, as an adjunct to this standard care, which will provide 6 weeks of ongoing text messaging support for quitting. This ongoing support includes continued and more intensive education regarding nicotine dependence, quitting smoking, and relapse; does not require additional agency resources; can be available “on demand” to the user; and includes features to personalize the quitting experience. During the field period, each drop-in center will alternate in delivering these two treatments, offering one group-based smoking cessation counseling session every other month (to reduce possible contamination between conditions), with the type of treatment delivered first at each drop-in center being randomly determined. This pilot study will investigate whether receiving the TMI adjunct to standard smoking cessation care results in greater reductions in cigarette smoking compared to standard care alone over a 3-month period.

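### The stated 80% power at h = 0.72 does not quite follow from its own inputs (78%, or h of about 0.74), and moderate is a misleading label for that effect

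*Protocol article*

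**What the plan says.** The sizing statement is in the protocol article under Power Considerations. Its inputs are:

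- Enrolment and cluster size: "we plan to enroll up to 80 participants, with approximately 5–7 participants per group or cluster".
- Allocation, from the Overview: "Half of these smokers will then also receive the TMI", so 40 per condition.
- Retention: "We assume that 90% of them participate in the follow-up survey", so 36 per condition.
- Clustering: "assume a conservative interclass correlation (ICC) of 0.05".

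The section then reports an effective sample size of 28.8 per condition ("Under these assumptions, the effective sample size (ESS) at follow-up will be" introduces the formula) and concludes: "This provides 80% power to detect a moderate quit rate effect size". The effect is given only as Cohen's h: "h = 0.72) for the difference between the two treatment conditions (alpha = 0.05". No control quit rate is given, h is not translated into quit rates, and the sidedness of alpha is not stated.

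The only effect-size evidence for text messaging in the article is in the background section on TMIs, which reports from a meta-analysis that "TMIs increased quit rates by 50–60"%, including when the messaging was added to other cessation support.

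**The concern.** There are two separate problems. First, the three quantities in the power sentence (effective sample size, power and h) should fit one another under a standard formula, and they do not quite. Second, a reader who is told that the trial has 80% power for a moderate effect will picture a realistic improvement in quitting. On the quit-rate scale h = 0.72 is a very large improvement, well above what the article's own background suggests.

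This paragraph is the only quantitative justification of the sample size. If it stands, a non-significant pilot result could be taken as evidence against the intervention, although the trial would have had little chance of detecting an effect of the size the background cites.

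**Working it through.** **1. Effective sample size.** 80 × 0.90 / 2 = 36 per condition. With 6 per cluster and ICC 0.05, the design effect is 1 + 5 × 0.05 = 1.25, and 36 / 1.25 = 28.8. This reproduces the article's figure exactly.

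**2. Power at h = 0.72.** Arcsine normal approximation, two-sided alpha 0.05 (assumed):

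- Power = Φ(h·√(n/2) − 1.960) = Φ(0.72 × √14.4 − 1.960) = Φ(2.732 − 1.960) = Φ(0.772) = 78.0%.
- Detectable h at 80% power = (1.960 + 0.842) / √14.4 = 2.802 / 3.795 = 0.738.
- Effective n needed for h = 0.72 = 2 × (2.802 / 0.72)² = 30.3 per condition.

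Varying the inputs does not recover the stated pair exactly:

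| Variant | Effective n | Power at h = 0.72 | h at 80% power |
|---|---|---|---|
| Cluster size 5 | 30.0 | 79.6% | 0.723 |
| Cluster size 5.4 (6 less 10% loss) | 29.5 | 79.0% | 0.729 |
| Cluster size 6 (as stated) | 28.8 | 78.0% | 0.738 |
| Cluster size 7 | 27.7 | 76.4% | 0.753 |
| Cluster size 6, one-sided alpha | 28.8 | 86.2% | 0.655 |

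**3. Design caveat: few sessions.** About 80 / 6 ≈ 13 sessions carry the comparison. Suppose the test used session-level degrees of freedom, about 9 to 12 (an assumption), and all of the 0.05 ICC lay within center. A noncentral t with noncentrality 2.732 then gives 68% power (9 df) to 71% (12 df) at h = 0.72, and the detectable h becomes 0.83 to 0.80.

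The site terms promised in the Discussion work in the other direction. If half the ICC lay between centers (assumed), the effective n would be 36 / (1 + 5 × 0.025) = 32; if all of it did, 36. Power at h = 0.72 would then be 82% and 86% with normal critical values, or about 73–75% and 78–80% with 9–12 df.

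**4. What h = 0.72 means.** p₂ = sin²(arcsin√p₁ + h/2), with the control rate p₁ assumed:

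| Control rate | Intervention rate at h = 0.72 | Ratio | Intervention rate at h = 0.738 |
|---|---|---|---|
| 5% | 30.5% | 6.1 | 31.4% |
| 10% | 39.7% | 4.0 | 40.6% |
| 20% | 53.8% | 2.7 | 54.7% |
| 30% | 65.2% | 2.2 | 66.0% |

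**5. Power for the effect cited in the background.** h = 2·arcsin√p₂ − 2·arcsin√p₁, effective n = 28.8, two-sided, normal approximation:

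| Control rate | h for a 50–60% relative increase | Power |
|---|---|---|
| 10% | 0.15–0.18 | about 9–10% |
| 20% | 0.23–0.28 | 14–18% |
| 30% | 0.31–0.37 | 22–29% |

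**6. Precision.** The 95% half-width for the difference in quit rates is 1.96 × √(2p(1 − p)/28.8). With 10% in both arms this is 1.96 × √0.00625 = 0.155, about 15 points. With 20% in both arms it is 1.96 × √0.01111 = 0.207, about 21 points.

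**The case against.** The strongest reply is that this is a pilot, the numerical gap is two points, and no decision turns on it. Much of that stands. A shift in h from 0.72 to 0.738 changes nothing in the design, and cluster size 5, which is within the stated range, nearly closes the gap. The section on smoking-behavior effects makes assessing promise and obtaining preliminary effect sizes the primary goal and expects some analyses to be descriptive. Power Considerations itself opens with estimation for a larger study. The cited meta-analysis covers studies with follow-up of 6 months or longer, mostly in general adults, so it is not a design value for a 3-month outcome in this population.

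Three stronger readings are tempting but are not supported:

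- **That true power is only 68–71%.** This needs a session-level t reference. The article makes the individual the unit of analysis, names logistic regression and adds site fixed effects; the reference distribution could properly be left to an analysis plan. The figure also gives no credit for between-center variance that the site terms may remove.
- **That the trial needs a quadrupled quit rate, or has 10% power for the expected effect.** Both depend on an assumed 10% control rate. The multiple runs from 6.1 at 5% to 2.2 at 30%.
- **That the investigators will treat a null result as evidence of no effect.** Nothing in the article says so. The risk is that a reader would do so.

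What the reply does not remove is that the stated pair fails to match its own effective sample size, and that *moderate* does not describe an effect that at least doubles the quit rate at every control rate tried here.

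**Conclusion.** The point holds as a correction of wording, of minor to moderate severity. On the article's own inputs, two-sided alpha and a normal approximation, power at h = 0.72 is 78%, and 80% power corresponds to h of about 0.74. The size of that discrepancy is trivial.

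The label is the more consequential defect. At assumed control rates from 5% to 30%, h = 0.72 is an absolute gain of roughly 25 to 35 points, and power for the relative increase cited in the background stays below 30% at the 10%, 20% and 30% control rates. That conclusion does not hinge on any one control rate.

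The session-level figures (power about 68–71%, detectable h about 0.80–0.83) are a conditional caveat, not a demonstrated shortfall. Low power is ordinary for a pilot of up to 80 and is not itself a fault.

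**What to change.** Revise the Power Considerations paragraph:

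- State the detectable effect as h of about 0.74 at 80% power, two-sided alpha 0.05, normal approximation. Add that it is about 0.8 if session-level degrees of freedom are used and the ICC lies within center.
- Show that effect as quit rates over several assumed control rates, for example 10% to about 41%, 20% to about 55% and 30% to about 66%.
- Delete *moderate*.
- Say that power is low for a 50–60% relative increase, giving the control rate beside each power figure.
- Give the expected 95% half-width for the difference in quit rates (about 15 points at 10% in both arms, 21 points at 20%) as the sizing rationale, and say that a non-significant result will not be read as lack of promise.

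The cost is wording only, and the stated figure becomes slightly less favorable. No participants, procedures or analyses change.
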